### Randomisation

In four of the Medicare Locals/Divisions of General Practice, enrolled general practices are randomly allocated to the control group or Intervention 1 at a ratio of 1:2. In the other three Medicare Locals/Divisions of General Practice, practices are randomly assigned to the control group or Intervention 2 at a ratio of 1:2. A single type of intervention is tested in each Medicare Local/Division of General Practice as a result of two practical constraints: (1) care facilitators included in Intervention 2 are required to work with four or five practices within a single geographic area in order to work effectively; and (2) Medicare Locals/Divisions of General Practice would find it difficult to enrol and support practices using two different interventions, given that Intervention 1 and Intervention 2 comprise multiple components. Randomisation is applied after recruiting each group of three practices in a combined Medicare Local/Division of General Practice and Region stratum, where Region refers to urban or rural area. This helps to mitigate the potential bias created by testing only one intervention in each Medicare Local/Division of General Practice. Randomisation is applied separately for urban and rural practices within each Medicare Local/Division of General Practice because it is expected that service use and availability will differ by region. To approximate equality of sample sizes in each group, block randomisation is used with computer-generated, randomly permuted blocks of three. A researcher who is not involved in the implementation of the project and is blinded to the identity of the practices performs this task.

### Study population

#### Practice inclusion criteria

All practices situated within the Medicare Locals/Divisions of General Practice that have agreed to take part in the study (located in South Australia, Queensland and Victoria, Australia) are offered an opportunity to participate in the project, conditional on meeting the following criteria: (1) the practice has not indicated that they will not participate in trials; (2) practice software (GPs’ desktop application) is compatible with project software for data extraction purposes; (3) the practice meets the Royal Australian College of General Practitioners (RACGP) definition of ‘general practice’; (4) the practice is accredited (or registered for accreditation) against the current edition of the RACGP ‘Standards for general practices’; (5) the practice has current public liability insurance; and (6) all health professionals at the practice who will be providing care to enrolled patients are appropriately qualified and registered, and have current professional indemnity insurance. Most general practices meet these criteria.

#### Participant inclusion criteria

Adult patients of participating general practices are eligible to participate in the trial if they meet the following criteria: (1) they are aged 18 years or older; (2) they have established (≥12 months duration) type 1 diabetes mellitus or newly diagnosed or established type 2 diabetes mellitus; and (3) they have the capacity to provide informed consent to participate.

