**Figure 2 F2:**
[figure not shown]
**Overview of risk stratification categories**^**#**^**.** HbA1c = Glycosylated haemoglobin; SBP = Systolic blood pressure. ^#^These risk stratification categories apply to participants with type 2 diabetes. Participants diagnosed with type 1 diabetes will be provided with the same level of resources as persons in the ‘out-of-range/complex’ category. Newly diagnosed patients will receive the support designated from their category plus additional support for introductory needs.

The altered funding arrangements that are tested in Intervention 2 comprise three components: flexible funding for general practices; pay-for-performance payments for general practices; and flexible funding for allied health professionals. Flexible funding for general practices provides upfront, lump sum funding for all patients who are voluntarily enrolled in the trial at a given practice, which is adjusted according to the risk of the patient population. This funding is used to fund care planning activities for those patients who require it (and is paid once a patient is enrolled rather than for completion of any specific activities) but it does not replace usual GP consultation fees covered by Medicare (Australia’s universal healthcare system). Pay-for-performance payments reward practices for improvements in patient clinical outcomes, meeting pre-defined levels of positive patient experience and completing pre-defined clinical processes. Flexible funding for allied health professionals is accessed on a fee-for-service basis, drawing on a risk-adjusted allowance for each patient. Participants in the control group, Intervention 1 and Intervention 2 will receive their respective care for a period of approximately 18 to 22 months (depending on when they are risk stratified).

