### Outcome measures

#### Primary outcome

The primary endpoint is the difference in the change in HbA1c between groups. The study is powered to detect a difference of at least 0.25 percentage points in mean HbA1c between any two treatment groups. This difference is considered clinically significant on an intention-to-treat basis [20]. HbA1c data is collected by practice staff, as directed by the care plan, and recorded in cdmNet.

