### Sample size calculation

A minimum sample size of 150 practices (or 50 practices per trial arm) and 3,750 patients (or 1,250 patients per trial arm) would allow a difference of 0.25 percentage points of HbA1c to be detected between any two trial arms with 80 percent power. The sample size is based a standard deviation of HbA1c of 1.4 percent, 20 percent attrition over 18 months, a design effect of 3.45 based on an ICC of 0.05 (correlation between baseline and 18-month HbA1c), and a two-sided alpha level set at 0.025 to adjust for pairwise comparisons.

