### Statistical analysis

#### Main analysis

Descriptions of participants’ baseline characteristics (e.g., demographic data, comorbidities and clinical metrics) will be reported by treatment group. Categorical variables will be summarised by frequencies and percentages. Continuous variables will be summarised by means and SEMs, or non-parametric equivalents. All primary statistical analyses will be performed on an intention-to-treat basis. The continuous variable—HbA1c at approximately 18 to 22 months—will be compared between groups using a linear mixed effect model with adjustment for clustering and stratification status (Medicare Local/Division of General Practice and metro/rural practice location). The time/group interaction parameter will be used to formally test for an intervention effect. Secondary outcomes (excluding economic sustainability and value for money) will be analysed similarly. These findings will be presented in accordance with the reporting requirements outlined in the Consolidated Standards of Reporting Trials (CONSORT) statement - extension for cluster randomised trials [21].

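### Patients enrol after their practice is randomised, so the newly diagnosed share could differ systematically by arm, and the stated primary model has no term to absorb it

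*Protocol article*

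**What the plan says.** All places are in the protocol article.

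- **Participant inclusion criteria:** patients qualify if "they have established (≥12 months duration) type 1 diabetes mellitus or newly diagnosed or established type 2 diabetes mellitus". Type 1 carries a minimum duration and type 2 carries none. The article does not define newly diagnosed.
- **Primary outcome:** "The primary endpoint is the difference in the change in HbA1c between groups". The design target is stated there: "The study is powered to detect a difference of at least 0.25 percentage points in mean HbA1c between any two treatment groups".
- **Main analysis:** HbA1c is compared "using a linear mixed effect model with adjustment for clustering and stratification status (Medicare Local/Division of General Practice and metro/rural practice location"), and the effect is tested by the time-by-group interaction. Diabetes type and duration are not among the named terms.
- **Randomisation:** the strata are Medicare Local/Division and urban or rural location. Neither carries information on type or duration.
- **Recruitment:** practices are randomised, then trained in their assigned arm. Eligible patients are written to and telephoned, and the caller may be the care facilitator.
- **Interventions:** the care facilitator, the lump sum paid when a patient enrols, and the payments for improved clinical outcomes belong to Intervention 2 only.
- **Discussion:** enrolment of patients after practice randomisation is acknowledged as a drawback and defended on practical grounds. The only correction promised there concerns bias between Medicare Locals/Divisions.

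**The concern.** Randomising practices balances, in expectation, the patients a practice already has. It does not balance which of them enrol once the practice knows its arm. In Intervention 2 the person encouraging enrolment may be part of the intervention, and the practice gains financially from enrolling patients and from their improvement. Patients who are likely to improve are therefore worth more to that arm. Recently diagnosed type 2 patients, whose HbA1c may fall once treatment begins under any model of care, are a plausible group of this kind.

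If their share differs systematically, the arms have different expected HbA1c trajectories even when neither care model has any effect. A baseline table need not show this, because arms can agree on mean baseline HbA1c and still differ in expected change. The time-by-group term would take up the difference and report it as treatment effect. The trial is meant to inform national funding policy, and the arm with the clearest enrolment incentive is also the one that would need the largest system change.

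**Working it through.** **Inputs from the article.** Target difference 0.25 HbA1c points; SD 1.4 and 20% attrition ("a standard deviation of HbA1c of 1.4 percent, 20 percent attrition over 18 months"); two-sided alpha 0.025; power 80%; 1,250 patients per arm, hence 1,250 × 0.8 = 1,000 completers; ICC 0.05; stated design effect 3.45.

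**Inputs assumed, because the article gives neither.** Systematic difference in newly diagnosed share, Δp = 5 to 10 percentage points. Excess HbA1c fall in newly diagnosed over established patients, d = 0.5 to 1.5 points.

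**1. The plan's own figure.** The unclustered size is 2 × 1.4² × (2.241 + 0.842)² / 0.25² ≈ 597 per arm. Multiplying by 3.45 gives about 2,060, and dividing by 0.8 gives about 2,575, against 1,250 stated. The stated size is not reproduced from the stated inputs. That is a separate matter. Here it means that the standard error has to be shown over a range:

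- implied by the claimed 80% power: 0.25 / (2.241 + 0.842) = 0.081
- 1,000 completers, 25 patients per practice (design effect 1 + 24 × 0.05 = 2.2): 1.4 × √(2 × 2.2 / 1,000) = 0.093
- 1,000 completers, design effect 3.45: 1.4 × √(2 × 3.45 / 1,000) = 0.116

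**2. Bias from a systematic share difference.** Bias = Δp × d.

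| Δp | d = 0.5 | d = 1.0 | d = 1.5 |
|---|---|---|---|
| 5 points | 0.025 (10% of 0.25) | 0.05 (20%) | 0.075 (30%) |
| 10 points | 0.05 (20%) | 0.10 (40%) | 0.15 (60%) |

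To imitate the whole 0.25, Δp would have to be 0.25 / d: 50, 25 or 16.7 percentage points.

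**3. Effect on the test.** With bias b, the true two-sided error is 1 − Φ(2.241 − b/SE) + Φ(−2.241 − b/SE), nominally 0.025.

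| b | SE 0.081 | SE 0.093 | SE 0.116 |
|---|---|---|---|
| 0.025 | 0.032 | 0.030 | 0.028 |
| 0.05 | 0.054 | 0.047 | 0.039 |
| 0.10 | 0.157 | 0.123 | 0.085 |
| 0.15 | 0.348 | 0.266 | 0.171 |

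**4. Chance imbalance, for contrast.** The SD of the share difference is √(2p(1 − p) × DE / 1,000). For assumed shares p of 2% to 10% and design effects DE of 2.2 to 3.45, it runs from 0.9 to 2.5 percentage points. At d = 1.5 this moves the estimate by 0.014 to 0.037. That is small against 0.081 and already part of sampling error.

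**5. Variance from pooling.** The added variance is p(1 − p)d². For p = 5% and d = 1.0 it is 0.0475, about 2% of 1.4² = 1.96. For p = 10% and d = 1.5 it is 0.2025, about 10%. The article does not give the SD of change, so these are only orders of magnitude.

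**The case against.** The strongest reply is that the article contains no error of eligibility. Broad entry suits a pragmatic trial, and further covariates or sensitivity analyses may stand in an analysis plan that is not shown. The article also does not say that its list of adjustments is exhaustive. The eligibility point stands, and no change of eligibility is asked for. On the model, however, the article does more than stay silent: it names the adjustment set for the primary test, and the comment is on that set. If the analysis plan already adds these terms, the point is met.

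A second reply is that recruitment is described as one procedure for all arms (identify, write, telephone) and that the drawback is disclosed. Both are true. But the caller and the payments differ by arm, and disclosure comes with no analytic remedy for differential patient enrolment.

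Three stronger readings are tempting, and the article does not support them:

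- **Any difference in share is read as effect.** It is not. Practices are randomised within strata, and the test allows for chance imbalance.
- **The intervention tools raise case-finding.** The population reports are described as covering people already enrolled, and no payment is tied to making a diagnosis. The payment incentive exists in Intervention 2 only, so the route is weaker for Intervention 1 against control.
- **The extra introductory support shows bias.** The note to Figure 2 says "Newly diagnosed patients will receive the support designated from their category plus additional support for introductory needs", but under Intervention 2's risk stratification this is part of the intervention. A fall that it causes is a real effect.

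It also stands that the size rests wholly on assumed inputs. The assumed share gaps exceed what chance alone would usually produce, and no figure in the article shows that such gaps will occur.

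**Conclusion.** The point holds in a limited form. The design leaves a documented route, mainly in Intervention 2, by which the newly diagnosed share could differ systematically between arms. The stated primary model has no term to keep such a difference out of the time-by-group parameter. This is a risk, not a demonstrated bias. It needs two conditions that the article neither states nor excludes: arm-dependent enrolment of newly diagnosed patients, and a larger fall in HbA1c among them than among established patients.

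Under the assumed ranges the bias cannot by itself imitate the target effect. It can still distort the test: a systematic 0.05 points would roughly double the error rate from 0.025 to 0.054 at the standard error the plan claims, and raise it to 0.039 at the largest standard error considered. If either condition fails, the bias is zero and the added terms cost little. The change is worth making because it is cheap and protects the primary parameter.

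**What to change.** In Main analysis, add two baseline factors to the primary model, each interacted with time: diabetes type, and newly diagnosed versus established status at the patient's own baseline. Define the status from the diagnosis date in the GP record, obtained the same way in all three arms, with the cut-off in months fixed before the data are analysed.

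Add one sensitivity analysis limited to patients diagnosed before their practice was randomised. This removes anyone whose diagnosis followed allocation. It does not remove selective enrolment of patients diagnosed shortly before, so it supplements the adjustment and does not replace it. Keep eligibility unchanged.

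Report the newly diagnosed share by arm among enrolled patients, so that readers can see whether the concern arose.

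The cost is a few degrees of freedom, with some possible gain in precision, and one further data item. The diagnosis date must be extracted in every arm: eligibility does not require the duration of type 2 disease, and the article shows newly diagnosed status being used only in Intervention 2. The adjustment deals with this one source of differential enrolment. Selection on other patient characteristics remains under the drawback that the Discussion already acknowledges.

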#### Participant exclusion criteria

Patients are excluded from the study if one or more of the following criteria are present: (1) they have a terminal illness with a life expectancy of less than two years; (2) they have dementia; (3) they are pregnant or planning to become pregnant in the next two years; and (4) they are participating in the Coordinated Veterans Care (CVC) program.

### Interventions

Each general practice (cluster) is randomly assigned to one of the three treatment arms. Participants in the control group are assigned ‘usual care’, meaning that practices will continue to provide care as usual.

Practices assigned to Intervention 1 experience two changes: access to an online chronic disease management network (cdmNet) and access to training and capability building. The cdmNet decision support service is instrumental in generating, updating and reviewing multidisciplinary care plans; facilitating communication between team members; sharing patient information; engaging patients in their care; and facilitating service payments. The care plans generated by cdmNet in Intervention 1 are pre-populated with the minimum care requirements for the general diabetes population, as informed by best practice guidelines and recommended treatments for any recognised comorbidities. CdmNet also generates population-level clinical status reports that allow GPs to proactively manage their population of people with diabetes enrolled in the trial. The training and capability building has three main functions: to assist practices in implementing the new model of care and cdmNet; to provide regular access to endocrinologists/diabetologists; and to provide a forum where practices can find out about new developments in diabetes care and share their experiences with other trial participants.

Practices assigned to Intervention 2 experience four changes: access to cdmNet; altered funding arrangements; the provision of a care facilitator; and access to training and capability building. Coordinated care is facilitated through the use of the cdmNet decision support service (as in Intervention 1), but with the addition of risk stratification. Patients are stratified into one of four risk categories based on whether they have complications associated with diabetes (e.g., peripheral neuropathy, background diabetic retinopathy, foot ulceration) and whether their diabetes is under control (uncontrolled diabetes requiring additional allied health services is defined as either HbA1c >7.5% [>58.5 mmol/mol], systolic blood pressure >150 mmHg, total serum cholesterol >5.0 mmol/l, or systolic blood pressure >140 mmHg plus total serum cholesterol >4.5 mmol/l). The four risk categories are characterised as follows: (1) not complex and within range; (2) complex and within range; (3) not complex and out of range; and (4) complex and out of range (see Figure 2). The care plan that is generated for the patient reflects the minimum care needs of individuals in their respective strata, as informed by best practice guidelines. Care in Intervention 2 is also coordinated through the provision of a full-time care facilitator (a tertiary-qualified health professional with experience in primary health care delivery), whose role is to assist the multidisciplinary team in delivering care in accordance with the agreed care plan. The care facilitator has a case load of approximately 300 to 400 patients across all four risk strata.

**Figure 2 F2:**
[figure not shown]
**Overview of risk stratification categories**^**#**^**.** HbA1c = Glycosylated haemoglobin; SBP = Systolic blood pressure. ^#^These risk stratification categories apply to participants with type 2 diabetes. Participants diagnosed with type 1 diabetes will be provided with the same level of resources as persons in the ‘out-of-range/complex’ category. Newly diagnosed patients will receive the support designated from their category plus additional support for introductory needs.

The altered funding arrangements that are tested in Intervention 2 comprise three components: flexible funding for general practices; pay-for-performance payments for general practices; and flexible funding for allied health professionals. Flexible funding for general practices provides upfront, lump sum funding for all patients who are voluntarily enrolled in the trial at a given practice, which is adjusted according to the risk of the patient population. This funding is used to fund care planning activities for those patients who require it (and is paid once a patient is enrolled rather than for completion of any specific activities) but it does not replace usual GP consultation fees covered by Medicare (Australia’s universal healthcare system). Pay-for-performance payments reward practices for improvements in patient clinical outcomes, meeting pre-defined levels of positive patient experience and completing pre-defined clinical processes. Flexible funding for allied health professionals is accessed on a fee-for-service basis, drawing on a risk-adjusted allowance for each patient. Participants in the control group, Intervention 1 and Intervention 2 will receive their respective care for a period of approximately 18 to 22 months (depending on when they are risk stratified).

### Outcome measures

#### Primary outcome

The primary endpoint is the difference in the change in HbA1c between groups. The study is powered to detect a difference of at least 0.25 percentage points in mean HbA1c between any two treatment groups. This difference is considered clinically significant on an intention-to-treat basis [20]. HbA1c data is collected by practice staff, as directed by the care plan, and recorded in cdmNet.

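### The primary test is of change in HbA1c, but the trial is sized on the SD of HbA1c itself with no usable baseline-to-end correlation, and 1,250 per arm does not give 80% power even at that SD

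*Protocol article*

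**What the plan says.** Three sections of the protocol article bear on this.

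- Primary outcome: "The primary endpoint is the difference in the change in HbA1c between groups". The next sentence refers to a difference in means: "The study is powered to detect a difference of at least 0.25 percentage points in mean HbA1c between any two treatment groups".
- Main analysis: "HbA1c at approximately 18 to 22 months—will be compared between groups using a linear mixed effect model", adjusted for clustering and the stratification factors. Then: "The time/group interaction parameter will be used to formally test for an intervention effect". Baseline HbA1c is not listed as a covariate, and the article does not say whether baseline means are constrained to be equal.
- Sample size calculation: 50 practices and 1,250 patients per arm "would allow a difference of 0.25 percentage points of HbA1c to be detected between any two trial arms with 80 percent power". The inputs are an SD of HbA1c of 1.4, 20% attrition, a design effect of 3.45 and two-sided alpha of 0.025. The design effect is said to rest on "an ICC of 0.05 (correlation between baseline and 18-month HbA1c").

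The Secondary outcomes section says all outcomes are measured at baseline and again at the end of the trial, so the model has two time points.

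**The concern.** With two time points and free baseline means, the time/group interaction is the between-arm difference in change. Its precision depends on the SD of change, and so on the correlation r between a patient's baseline and final HbA1c. The sample size section gives the SD of the HbA1c value and no SD of change. The one figure it labels as a baseline-to-end correlation is the 0.05 that also serves as the ICC. The power statement is therefore not tied to the test that will be run.

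A null result could not be read against the stated 80%. The wording also leaves room to choose later between a comparison of end values and a comparison of changes.

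**Working it through.** **Inputs** (Sample size calculation): difference 0.25; SD 1.4; two-sided alpha 0.025 (z = 2.241); power 80% (z = 0.842); design effect (DE) 3.45; attrition 20%; 1,250 per arm in equal arms, hence 1,250 × 0.8 = 1,000 completers per arm. The values of r below are assumptions, because the article gives no usable one.

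**1. The plan's own figure.** Unclustered n per arm = 2 × (2.241 + 0.842)² × (1.4/0.25)² ≈ 596. Multiplied by 3.45 this is about 2,057; divided by 0.8 it is about 2,570 per arm, against the stated 1,250.

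Power with 1,000 completers: effective n = 1,000/3.45 = 289.9. The standard error is 1.4 × sqrt(2/289.9) = 0.1163, and 0.25/0.1163 = 2.150. Power = P(Z > 2.241 − 2.150) ≈ 46%. The difference detectable with 80% power is 3.083 × 0.1163 ≈ 0.36.

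**2. Design effect.** 1 + (m − 1) × 0.05 = 3.45 gives m = 50 patients per practice, but 1,250/50 = 25. At 25 per practice, DE = 1 + 24 × 0.05 = 2.2. That needs 596 × 2.2/0.8 ≈ 1,640 per arm and gives 67% power at 1,250. With 20 completers per practice, DE = 1.95 and power is 73%. All are below 80%.

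**3. The contrast tested.** SD of change = 1.4 × sqrt(2(1 − r)), which equals 1.4 only at r = 0.5. SD of the end value adjusted for baseline = 1.4 × sqrt(1 − r²), which never exceeds 1.4. A time/group model with baseline means constrained to be equal has the same factor, 1 − r². Power = P(Z > 2.241 − 2.150/sqrt(factor)) at DE 3.45, where the factor is 2(1 − r) or 1 − r²; at DE 2.2, 2.692 replaces 2.150.

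| r (assumed) | SD of change | Power, change, DE 3.45 | Power, change, DE 2.2 | Adjusted SD | Power, adjusted, DE 3.45 | Power, adjusted, DE 2.2 |
|---|---|---|---|---|---|---|
| 0.3 | 1.66 | 34% | 51% | 1.34 | 51% | 72% |
| 0.5 | 1.40 | 46% | 67% | 1.21 | 60% | 81% |
| 0.7 | 1.08 | 70% | 89% | 1.00 | 78% | 94% |

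**4. Correlation needed for 80%.** At DE 3.45 the SD must not exceed 0.25 × sqrt(289.9/2)/3.083 = 0.976. For change, r = 1 − (0.976/1.4)²/2 ≈ 0.76. For the adjusted analysis, r = sqrt(1 − (0.976/1.4)²) ≈ 0.72. At DE 2.2 the largest SD is 1.222, and the two thresholds are about 0.62 and 0.49.

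**The case against.** **The model may not be the unconstrained one.** The article does not say that baseline means are free. A constrained model has the 1 − r² factor, and a condensed article may leave this to the analysis plan. This stands: the loss of efficiency is conditional on the model. It does not supply the missing correlation or repair the power figure.

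**A correlation may have been used and lost in condensing.** The stated inputs with r = 0.76 for change give 1,238 per arm, close to 1,250. This can be neither confirmed nor excluded. If it is so, that figure needs to be printed, because the printed text attaches the description to 0.05.

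**The two quantities agree in expectation.** Under randomisation, a difference in end means and a difference in changes have the same expected value. That is fair for the comparisons with control, so the wording is loose and does not set up two conflicting treatment effects. Their variances still differ, and power depends on variance.

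**Change may be the safer choice here.** Patients enrol after practices are randomised (Discussion), and Interventions 1 and 2 are tested in different Medicare Locals (Randomisation). Systematic baseline differences are possible, and adjusted and change analyses could then disagree. This stands as a real cost of making the adjusted analysis primary.

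**Stronger readings the article does not support.** A reader might take r of at least 0.5 as enough to secure 80% power. It is not, because the inputs give 46% at SD 1.4. A reader might also take 0.05 literally as the correlation, giving an SD of change of 1.93 and about 25% power. The same number is called an ICC and used for the design effect, so a mislabelled within-practice ICC is the likelier explanation, and the 25% should not be presented as the trial's power.

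**Conclusion.** The point holds as a mismatch between the contrast tested and the quantity used to size the trial, on top of a sample size that does not follow from its own inputs. The stated inputs need about 2,570 per arm and give 46% power at 1,250.

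Over an assumed r of 0.3 to 0.7 at the stated design effect, power is about 34% to 70% for the unconstrained change test and 51% to 78% for the baseline-adjusted one. The stated 80% is reached only at r of about 0.76 or 0.72 respectively, or 0.62 or 0.49 at a design effect of 2.2.

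These figures assume equal arms, equal SDs at both times, and the same design effect for change as for the value. The last is uncertain: stable practice effects cancel in change, and no ICC of change is given.

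The article does not show that the trial is unable to detect 0.25. With a high enough correlation it could. It shows that the stated power has no printed basis for the test named.

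**What to change.** 1. **Sample size calculation.** Describe 0.05 as the within-practice ICC, if that is what it is. State the baseline-to-end correlation or SD of change assumed, with its source. Restate power, or the detectable difference, at 1,250 per arm for the contrast actually tested, with a design effect that matches the patients per practice. Do not present SD 1.4 as making 1,250 per arm sufficient.
2. **Primary outcome and Main analysis.** Name one primary contrast. The preferred choice is end-of-trial HbA1c from the mixed model with baseline HbA1c as covariate (or a time/group model with baseline means constrained to be equal), a practice random effect and the stratification terms. Keep the unconstrained difference in change as a sensitivity analysis.
3. **Reporting.** State that baseline imbalance could make the two analyses differ, for the reasons of enrolment and allocation given above, and report both.

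The cost is wording and one recalculation, with no new data, because baseline HbA1c is already collected. The restated power may come out below 80%, and the article should then say so.
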